### Intervention and fidelity check

PE lessons were conducted twice a week over 4 weeks in both control and intervention conditions. In the control condition, PE teachers encouraged students to participate in PA during leisure time without delivering persuasive messages in PE lessons. An intervention program was implemented after the control period was over (see Fig. 2).

Prior to the intervention period, PE teachers were trained on how to deliver persuasive messages through a 3-h workshop. During the workshop, PE teachers were encouraged to express their concerns about delivering persuasive messages, researchers addressed those concerns to assist PE teachers to conduct the intervention at a sufficient level of proficiency. The persuasive messages targeted salient information related to the benefits and barriers associated with PA, which were identified based on the results of surveys conducted for students at Pre-Baseline in the control condition. Some examples of salient benefits were “health benefits”, “improving physical skills and fitness”, “fun and socialization” and “recommended physical activity level”, whereas salient barriers were “lack of time”, “lack of facilities or equipment”, “feeling tired” and “weather”.

In the intervention condition, PE teachers delivered the persuasive messages that targeted the salient benefits and barriers associated with PA at the last 5 to 10 min of each PE lesson. After PE teachers delivered the persuasive message, students were asked to answer a question about the message in each lesson (e.g., “Please explain briefly how do you know that MVPA improves your fitness levels?”). Researchers evaluated PE teachers’ fidelity of the interventions with a checklist (e.g., “The PE teacher provided clear instructions on this session’s message”) on a scale ranging from 1 (*not at all*) to 5 (*very much*).

### Outcome measures

Students’ BMI were calculated based on their height and body mass, and overweight or obese students were identified based on Cole et al.’s classification [23]. Students’ PA levels were measured objectively with GENEActiv (Original) accelerometers configured at 100 Hz, and subjectively with the International Physical Activity Questionnaire [24] (e.g., “During the last 7 days, how many days did you do vigorous physical activities?”),and the Leisure-Time Physical Activity Participation Questionnaire [25] (“How often did you do any regular activity long enough to sweat last week during your leisure time?”) on a 8-point scale ranging from 0 (*none*) to 7 (*every day*).

Students’ attitudes, intentions, subjective norms and perceived behavior control towards leisure-time PA were measured with a questionnaire based on the constructs from the TPB. Attitudes were assessed through five items with bipolar adjectives (enjoyable/unenjoyable, good/bad, useful/useless, interesting/boring, and beneficial/harmful) on a 7-point semantic differential scale [26]. Behavioral intentions were assessed with three items (e.g., “For the next 4 weeks, I intent to do vigorous physical activity for at least 3 times [*at least 30 minutes*] per week.”) based on a 7-point scale ranging from 1 (*unlikely*) to 7 (*very likely*) [19]. Subjective norms were assessed through three items (e.g., “Most people who are important to me think I should do vigorous physical activity for at least 3 times [*at least 30 minutes*] per week for the next 4 weeks.”) based on a 7-point scales ranging from 1 (*strongly disagree*) to 7 (*strongly agree*) [21]. Perceptions of behavior control were measured using three items (e.g., “I feel in complete control over doing vigorous physical activities for at least 3 times [*at least 30 minutes*] per week for the next 4 weeks.”) based on 7-point scale ranging from 1 (*completely false*) to 7 (*completely true*) [19].

Participants were also asked to compare intention, determination and willingness to engage in another activity during their leisure time with vigorous PA and answer three questions (e.g., “How much do you intend to do the other activity for at least 30 minutes, 3 times a week for the next 4 weeks during your leisure time?”) based on a 7-point scale, ranging from 1 (*not at all*) to 7 (*very much*).

Goal conflict and facilitation were assessed through five items (e.g., “To what extent is the other activity likely to prevent you from doing vigorous physical activity for at least 30 minutes, 3 times a week for the next 4 weeks during your leisure time?”) based on a 7-point scale ranging from 1 (*not at all*) to 7 (*very much*).

### Data analysis

To examine the first research hypothesis (*H*_*1*_), a 2 (type of conditions: control vs. intervention) × 3 (measurement points: Baseline, Post 1 and Post 2) repeated ANOVA will be conducted on students’ MVPA levels. The second hypothesis (*H*_*2*_) will be examined through a 2 (type of conditions: control vs. intervention) × 3 (measurement points: Pre-Baseline, Post 1 and Post 2) repeated ANOVA on students’ BMI levels. A path analysis will be conducted to examine the third hypothesis (*H*_*3*_) with *M*plus (Version 8) [27]. Student’s age, gender, socio-economic status, and prioritization of PA together with fidelity of intervention programs will be included as covariates in the analyses. Furthermore, correlation analyses will be conducted to examine the relationships between the subjective and objective measures of PA.

A cost effectiveness analysis of the program will also be conducted by focusing on the incremental cost-effectiveness of the intervention condition compared to the control condition. Incremental cost-effectiveness ratios will be calculated in terms of the incremental cost per unit BMI reduction. Differences in BMI between different measurement points (Pre-Baseline, Post 1 and Post 2) will also be calculated. Height will be added as a covariate in the analyses in order to account for the growth change in height over the data collection period. Incremental cost-effectiveness ratios will be calculated using standard techniques coupled with bootstrapping methodology and acceptability curves [28]. Through these analyses, it will provide information about the probability that an intervention is cost-effective.

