**Methods/design:**

A total of 171 students from 3 secondary schools in Singapore underwent the control condition followed by the intervention condition. Both the conditions consisted of PE lessons twice per week over 4 weeks. In the control condition, PE teachers encouraged students to participate in PA during leisure time without providing persuasive message. While in the intervention condition, PE teachers delivered persuasive messages that targeted the salient benefits and barriers associated with PA to the students at the last 5 to 10 min of each PE lesson. PA levels over a week were measured objectively with wrist-mounted GENEActiv Original accelerometers and subjectively with self-reporting questionnaires three times (Baseline, Post 1, and Post 2) in each condition. Student’s self-reported PA level was measured using the Leisure-Time Physical Activity Participation Questionnaire and the International Physical Activity Questionnaire, and their attitudes, intentions, subjective norms and perceived behavior control towards leisure-time PA were measured with a questionnaire based on the theory of planned behavior. Furthermore, students’ intention, determination and willingness to engage in leisure-time PA were compared with the other activity (e.g., doing homework, shopping).

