## Methods/design

### Study design

The Institutional Review Board at Nanyang Technological University (Singapore) provided ethical approval for the current study. Although the study was originally planned to conduct as a cluster-randomized controlled trial, the original plan had to be changed due to great difficulty in recruiting schools. This study adopted a 2 (type of conditions: control vs. intervention targeting salient PA benefits and barriers) × 3 (measurement points: Baseline, Post 1 and Post 2) within-subjects design in which all participants underwent the control condition followed by the intervention condition. Figure 2 provides the flow of the study design.

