### Participants

A total of 171 students aged 13 to 16 years old and attending co-educational secondary schools voluntary participated in the present study. All secondary schools in Singapore were invited to participate in the study via e-mail through publicly available contact details. The research team also attended a meeting with school principals to invite their schools to participate in the study. The three secondary schools whose principal granted permission were included in the study, and approval for data collection at the schools was also obtained from Singapore Ministry of Education. After the department head and PE teachers selected two classes at their school, a researcher attended their PE lessons and explained the risks and benefits of the study to the students by distributing information sheets and informed consent forms. They also had the opportunity to ask questions about the study requirements prior to completing and signing an informed consent form. Students were asked to pass the information sheets and informed consent forms to their parents and discuss their participation in the study with them. Students who gave their consent and returned the informed consent forms signed by their parent were eligible to participate in the study. Parents who consented were asked to complete a brief demographics and socioeconomic status questionnaire. Students who did not return the signed informed consent forms or could not participate in PE lessons were excluded from the study. They participated in PE lessons together with their classmates, but did not do any tasks for the study.

The pilot study by Chatzisarantis et al. [21] reported that their TPB-based intervention with mixed (between and within-subjects) design had a small effect on adolescents’ PA participation (ƞ_p_^2^ = .01) and large effects on their beliefs (ƞ_p_^2^ = .15). Therefore, a conservative small effect size of ƞ_p_^2^ = .02 (*f* = .14) was adopted to calculate the total sample size with G*Power version 3.1.9.2 [22]. It was estimated that a sample of 174 participants was required to achieve a power of .90 at the alpha level of .05 for the repeated within-subjects analysis of 6 groups (2 classes at three schools) and 6 measurement points (3 measurement points in two conditions).

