### Procedure

Prior to the commencement of the study in each condition, students’ body compositions (e.g., height, body mass and body fat percentage) were measured at their school. Height was measured using a ruler attached to the wall to the nearest 0.5 cm, body mass and body fat percentage were measured with a body composition monitor (Omron Karada Scan: HBF-362). Students were also asked to complete a demographics sheet and a set of self-report measures of leisure-time PA and psychological variables (Pre-Baseline). After completing the questionnaire set, students were instructed to wear the GENEActiv (Original) accelerometer (Activinsights Ltd, Cambridgeshire, UK) on their non-dominant wrist for one week to objectively measure frequency and intensity of their PA level (Baseline). When students returned the accelerometer, they were also asked to complete another set of the same self-report measures (Baseline). Subsequently, students spent four weeks in the control or intervention condition. During the 4 weeks, an intervention program was conducted in PE lessons in the intervention condition. After the 4 weeks, students were requested to wear the accelerometer again for one week across two occasions (Post 1 and Post 2) with a 4 weeks interval period in between before measuring their body compositions and completing the same set of self-report measures. Students’ height, body mass and body fat percentage were measured at three occasions (Pre-Baseline, Post 1 and Post 2) in each condition (see Fig. 2).

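### The repeated ANOVA for MVPA (H1) in its standard form keeps only students with all six measurements, and the sample size leaves no room for loss; a mixed model on all observed occasions is the better primary analysis

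*Protocol article*

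**What the plan says.** The Study design section describes a "within-subjects design in which all participants underwent the control condition followed by the intervention condition". Each condition has three measurement points. According to the abstract, "PA levels over a week were measured objectively with wrist-mounted GENEActiv Original accelerometers and subjectively with self-reporting questionnaires three times" in each condition, which makes six wear weeks per student. The Procedure section confirms the follow-up wears: "students were requested to wear the accelerometer again for one week across two occasions (Post 1 and Post 2").

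For H1, the Data analysis section opens with "To examine the first research hypothesis" and names the method, with two conditions and three "measurement points: Baseline, Post 1 and Post 2) repeated ANOVA will be conducted on students’ MVPA levels". H2 uses the same form of analysis on BMI, with Pre-Baseline in place of Baseline.

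On sample size, the Participants section says that "a conservative small effect size of ƞ_p_^2^ = .02 (*f* = .14) was adopted" and that "a sample of 174 participants was required to achieve a power of .90 at the alpha level of .05". The calculation assumed six groups and "6 measurement points (3 measurement points in two conditions"). No allowance for lost students or lost weeks is mentioned, and 171 students took part.

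**The concern.** A standard repeated ANOVA needs a full row of six values per student. A student with five good weeks and one missed week contributes nothing. Over six separate wear weeks in 13- to 16-year-olds, even a modest rate of missed weeks can remove many rows if the misses are scattered across students.

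Two things are at stake. The first is precision: the sample size assumes complete data, and enrolment is already 3 below it (174 − 171). The second is who is analysed. A complete-case result is generally safe only if missing weeks are unrelated to activity. A likelihood-based mixed model needs the weaker condition that missingness depends only on observed data. Non-wear related to activity is plausible here, although the article does not show it.

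**Working it through.** **Inputs from the Participants section.** Partial eta squared .02; k = 6 groups; m = 6 measurements; alpha .05; power .90; required N 174; enrolled 171. f² = .02/.98 = .0204, so f = .1429 (printed as .14).

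**The plan's own figure.** Take a noncentral F test for a within-subjects effect, with sphericity assumed and partial eta squared as reported by standard software:

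- λ = f²(N − k)(m − 1), df1 = m − 1 = 5, df2 = (N − k)(m − 1).
- The smallest N with power of at least .90 is 169 (power .901). Rounded up to a multiple of 6 groups, this is 174, as stated.
- With f rounded to .14, N is 176, close to the stated figure.
- At N = 171, power is .905 (f = .1429) or .892 (f = .14).

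So 174 reproduces, and it contains no inflation for loss.

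**The test that addresses H1.** The condition × time interaction has (2 − 1)(3 − 1) = 2 df. With λ = f² · 2 · (n − 1) and df2 = 2(n − 1), power at n = 171 is .647 with nothing missing. This drop from .90 comes from the change of test, not from missing data, so the two bases are kept apart below.

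**Missed weeks (assumed rates; the article gives none).** If each week is missed independently with probability p, the complete cases number 171(1 − p)^6. The total number of student-weeks is 171 × 6 = 1,026. Power uses f = .1429.

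| p | (1 − p)^6 | Complete students | 5-df power | 2-df power | Student-weeks used: complete-case / all observed |
|---|---|---|---|---|---|
| 0 | 1 | 171 | .905 | .647 | 1,026 / 1,026 |
| .05 | .735 | 126 | .77 | .51 | 754 / 975 |
| .10 | .531 | 91 | .60 | .38 | 545 / 923 |
| .15 | .377 | 64 | .42 | .28 | 387 / 872 |

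A quarter of students are lost at p = 1 − .75^(1/6) = 4.7%, and half at p = 1 − .5^(1/6) = 10.9%.

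**Misses that cluster within students.** Independence is close to the worst case.

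- Strong clustering (a student random intercept with SD 2 on the logit scale, simulated): 82% complete (about 140 students) at 5% missed weeks, and 69% (about 118) at 10%. The 5-df power is about .82 and .74.
- The same students miss every week: 171(1 − p) = 162, 154 and 145 students at 5, 10 and 15%. The 5-df power is .89, .87 and .84; the 2-df power is .62, .60 and .57. The lost students have no outcome at all, so a mixed model gains little.

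**The case against.** The strongest reply is that the article never states listwise deletion. That is the usual default of the method, but a fuller plan could set out imputation before the ANOVA, and the article's silence on missing data is not an error. This stands, so the point is confined to the method that the article does name and to a better alternative.

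A reader might infer more than the text supports:

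- **That much of the sample will be lost.** No missing rate is given. Large losses follow from scattered misses of about 5% or more per occasion, not from a few students who miss throughout.
- **That missing data alone take power far below the stated .90.** At 5% independent misses, the step from .90 to .65 is the switch from a 5-df to a 2-df test. Only .65 to .51 is due to missing data.
- **That unevenly spaced occasions break sphericity.** The Procedure section gives four weeks before Post 1 and a four-week interval before Post 2, so spacing within a condition is about even. The text does not give the gap between conditions.
- **That the same argument covers H2.** BMI comes from measurements taken at school. Those visits can be missed, but accelerometer non-wear has no bearing on them.
- **That a mixed model uses everything and removes bias.** Students with no outcome or with missing covariates, such as socio-economic status from the parent questionnaire, still drop out. If non-wear depends on that week's unobserved activity, the mixed model is biased too.

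The Data analysis section also does not say whether accelerometer or questionnaire MVPA enters the ANOVA. The Discussion points to the accelerometer data for a rigorous test of leisure-time MVPA. If questionnaire MVPA were used, missed wear weeks would not matter, although missed questionnaires would act in the same way.

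**Conclusion.** The concern holds in a conditional form, for H1. The article fixes a method that in its standard form needs six complete measurements per student, with a sample size that assumes no loss and 171 students against 174 required.

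At assumed independent miss rates of 5 to 15% per week, between 126 and 64 students remain, with the power losses tabulated above. At the other extreme, where the same students miss throughout, the loss is 5 to 15% of students and the choice of method matters little. The truth probably lies between, and the documents do not locate it. All power values assume partial eta squared .02 and sphericity.

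The change is worth making because the mixed model answers the same question, keeps partly observed students and rests on a weaker missing-data assumption. It should be made, but the article does not show that the trial fails without it.

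**What to change.** For H1, make the primary analysis a linear mixed model fitted by REML to all observed occasions. Use condition, time and condition × time as fixed effects, and test the same 2-df interaction. Use an unstructured, or similarly flexible, within-student covariance. A random intercept alone would impose compound symmetry, which is stricter than the sphericity assumed by the ANOVA. Name a simpler covariance as a fallback if the model does not converge.

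Keep the complete-case repeated ANOVA as a sensitivity analysis. State that the mixed model is valid under missing at random given the observed data, that it does not cover non-wear driven by that week's unobserved activity, and that students with no outcome or missing covariates remain excluded.

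The same model can be used for BMI (H2), for consistency and to handle missed measurement visits, but not on the ground of accelerometer non-wear.

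The cost is a change of wording, a few more modelling choices and the convergence fallback. No new data are needed, and the article still describes the analyses in the future tense.

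### The H1 and H2 ANOVAs have no error term for class, although teachers deliver the messages to six classes; if change is correlated within class, the tests overstate their precision

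*Protocol article*

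**What the plan says.** The Data analysis section tests H1 with a 2 (condition) × 3 (Baseline, Post 1, Post 2) "repeated ANOVA will be conducted on students’ MVPA levels". H2 uses the same form on BMI, with Pre-Baseline as the first time point. The covariates listed for the analyses are age, gender, socio-economic status, prioritization of physical activity and intervention fidelity; height is added in the BMI and cost-effectiveness work. No class, teacher or school term, random effect or cluster-adjusted error is named for either ANOVA.

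The Participants section describes how classes entered the study: "After the department head and PE teachers selected two classes at their school". There were three schools and 171 students. Under Intervention and fidelity check, PE teachers give the messages at the end of each lesson, and researchers rate how well each teacher does so.

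The authors knew of the grouping. Under Study design, "the study was originally planned to conduct as a cluster-randomized controlled trial", and the sample-size paragraph uses "6 groups (2 classes at three schools) and 6 measurement points (3 measurement points in two conditions". The class factor in that calculation does not reappear in the Data analysis section.

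**The concern.** Treatment is given to a class, so classmates share whatever is particular to their class in a given condition and week: how well their teacher delivers the message, an examination period, a school event, bad weather in the measurement week. A repeated ANOVA with only within-student factors takes its error from variation between students in how they change, and treats the 171 change profiles as independent. If changes are correlated within a class, about 28 students who share one influence are counted as about 28 separate confirmations of it.

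At stake are the p-values and confidence intervals for H1 and H2. The design assumes a small effect (partial eta-squared .02), so a moderate error in the standard error could change the conclusion, and one class's good month could look like a programme effect.

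**Working it through.** **1. The plan's own sample size.** "It was estimated that a sample of 174 participants was required to achieve a power of .90 at the alpha level of .05", with partial eta-squared .02, 6 groups and 6 measurement points (Participants section). Entering partial eta-squared directly in a within-factor repeated-measures F test:

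- f² = .02/.98 = .0204; df1 = 6 − 1 = 5; df2 = (N − 6) × 5; noncentrality λ = f² × df2.
- N = 168: df2 = 810, λ = 16.53, power .899. N = 169: df2 = 815, λ = 16.63, power .901.
- The minimum is 169, which rounds up to 174 for six equal groups. This matches the stated figure.

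The article does not state the program options, and some other settings also give 174. The figure is therefore reproduced as a student-level calculation with no design effect, but the match does not prove which options were used.

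**2. Inputs for the clustering check.**

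- Students: 171. Classes: 3 × 2 = 6. Mean class size m = 171/6 = 28.5 (Participants section).
- ICC of change between conditions and times: not in the document. Assumed .01 to .05, with 0 as the reference.

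**3. Formulas.** Design effect DE = 1 + (m − 1) × ICC = 1 + 27.5 × ICC. True SE / naive SE = √DE. Shortfall of the naive SE = 1 − 1/√DE. Effective N = 171/DE.

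| ICC of change | DE | True SE / naive SE | Naive SE too small by | Effective N |
|---|---|---|---|---|
| 0 | 1.00 | 1.00 | 0% | 171 |
| .01 | 1.28 | 1.13 | 11% | 134 |
| .02 | 1.55 | 1.25 | 20% | 110 |
| .05 | 2.38 | 1.54 | 35% | 72 |

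**4. Type I error of the planned test.** The effect of interest is the condition × time interaction, which has (2 − 1) × (3 − 1) = 2 numerator degrees of freedom. I simulated it under no effect, with 10,000 runs and classes of 29, 29, 29, 28, 28 and 28. The two interaction contrasts were independent, each with the stated ICC. Three analyses were compared at nominal 5%:

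- as planned, student-level error, 2 × (171 − 1) = 340 df;
- class added as a fixed between-subject factor, 2 × (171 − 6) = 330 df;
- F test on the six class means, 2 × (6 − 1) = 10 df.

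| ICC of change | As planned | Fixed class factor | Class means |
|---|---|---|---|
| 0 | 4.8% | 4.8% | 4.8% |
| .01 | 9.4% | 9.6% | 5.2% |
| .02 | 14.4% | 14.7% | 5.3% |
| .05 | 28.7% | 30.3% | 4.9% |

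The fixed class factor does not help, because its error term is still the variation between students within a class.

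**5. H2 in overweight students only.** The Aims section frames H2 on overweight students, while the Data analysis section refers to students' BMI in general. If only overweight students were analysed, with an assumed 5 to 10 per class, DE would run from 1 + 4 × .01 = 1.04 to 1 + 9 × .05 = 1.45. The inflation for H2 would then be smaller.

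**The case against.** The best defence is that each student is their own control, so class differences cancel. This holds for stable differences, which are usually the larger part. It does not hold for class-specific change, which is what enters the interaction.

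A second defence is that fidelity is measured and entered as a covariate, and fidelity belongs to the teacher. It may absorb part of the variation in delivery. It does not model the remaining correlation among classmates, and it does not cover events unrelated to delivery.

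A third is that the sample size already counts "6 groups (2 classes at three schools"). Even if class were carried into the ANOVA as a fixed factor, the simulation shows that the excess type I error would remain.

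A fourth is that a journal article condenses the plan. That would excuse silence, but here the article states the model and its factors. It is a fair reply for H3 and the cost-effectiveness analysis. A reader might infer that the path analysis and the bootstrap share the defect. The article gives no standard-error estimator for the first and no resampling unit for the second, so the document does not support that inference.

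Finally, no ICC of change is given. The size of the problem is therefore conditional, and it vanishes at 0.

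**Conclusion.** The point stands for the H1 and H2 ANOVAs. As stated, they have no error term for class or teacher, and they understate uncertainty whenever change is correlated within class. At an assumed ICC of .01 to .05 and 28.5 students per class, the naive standard error is 11% to 35% too small and the interaction test runs at about 9% to 29% instead of 5%. At an ICC of 0 the test is sound. These figures are a range under an assumption. A reader might take them as the trial's actual error rate, but nothing in the document fixes the ICC, so that reading is not supported. For H2 the effect is smaller if the analysis is confined to overweight students.

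The missing error term can be read directly from the Data analysis section; the magnitude cannot. The point should be acted on, because the change affects only the analysis and the article describes the analyses as still to be done.

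**What to change.** Analyse H1 and H2 with a linear mixed model that has student random effects and a random class-by-condition-by-time effect, using small-sample degrees of freedom (for example Kenward-Roger). Alternatively, analyse the six class-level difference-in-change estimates, the approach that held about 5% in the simulation. In either case, show the six estimates. State in the plan whether H2 covers all students or only overweight students.

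Three easier repairs should not be relied on. Class indicators leave the error term at student level. Standard cluster-robust errors are unreliable with six clusters. A bootstrap that resamples students within class holds the classes fixed and so omits the variation at issue. For H3 and the cost-effectiveness ratio, state that precision rests on six classes and give class-level results as a sensitivity check.

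The cost is wider intervals and few error degrees of freedom: 10 instead of 340 for the interaction test on class means. No new data are needed. The change does not remove the confounding of condition with calendar period, which comes from giving every class the control condition first.
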